### Intervention

The intervention is based on the TEACHOUT intervention [49]. It is comprised of a two-day training course (13 h in total) on EOtC for teachers who afterwards implement EOtC in 1–2 weekly sessions, a total of at least five hours per week, for one schoolyear (in this study, August 2022 to June 2023, Month 4 to 14, see Fig. 4). The EOtC sessions in the schools are delivered by one or more of the teachers across different school subjects in various places and settings outside the school buildings.

**Fig. 4 Fig4:**
[figure not shown]
The MOVEOUT study design

The course was structured to provide the teachers with knowledge and understanding of the theory and practice of EOtC. The course was taught by expert EOtC teachers and teacher education specialists and included theoretical lectures, supplemented by illustrative examples in workshops and videos, and plenum discussions on local implementation. The training course took place on the 28th and 29th of April 2022 (after randomisation, Month 0, see Table 1). The course was supplemented by two one-hour inspirational webinars during the first half of the school year (in this study, in September and November 2022, i.e., during Month 4 to 9, see Table 1).

Teachers in the control group received the two-day training course on EOtC in April 2023, close to the end of the intervention group implementation closeout; however, early enough for them to use the course content in their planning of the following school year. Also, they will receive the two one-hour inspirational webinars in the autumn 2023.

### Randomisation

Randomisation was performed by PE and MB on 1st of April 2022 (Month 0, see Fig. 4), and was made public on YouTube (see Supplementary Information, Additional file 1). Immediately after, the enrolled schools and teachers were informed by e-mail about the result of the randomisation process.

To ensure a balanced representation of grade levels across the intervention and control groups, stratified block randomisation in a 1:1 ratio was used (i.e., schools with participating classes in grade 4–6 and schools with classes 7–10 were randomised block wise in RStudio using the ‘dplyr’ and ‘readxl’ packages).

Due to the type of the intervention, it was not possible to blind the participants to group allocation. However, allocation levels will be coded before analyses and the analysts will not be informed about the codes before the final analyses have been performed.

### Sub-study 1: effects of EOtC

#### Design

Effects of EOtC will be measured in a between-subjects design. PA measurements pre- and post-intervention will be collected in two intervals each (Test A and B) to account for seasonal variations. Data collection of the first PA pre-intervention measure commenced before randomisation and continued until just before randomisation (Pre-test A, Month -2 to -1, see Table 1). The second PA pre-measure was collected after randomisation and before the implementation of the intervention (Pre-test B, Month -1 to 0). School motivation, wellbeing, and academic achievement were measured at pre-test B.

The first PA post-measure data collection will commence during the end of the school year (Post-test A, Month 10 to 11, see Table 1). The second PA post-measure data collection will be assessed immediately before finalisation of the intervention (Post-test B, Month 11 to 12, see Table 1). School motivation, wellbeing, and academic achievement will be measured at post-test B.

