### Aims

This study protocol outlines the design and methods of the MOVEOUT study. The objectives of the MOVEOUT study are to investigate the efficacy and mechanisms of the *TEACHOUT intervention* [49] (hereafter, the intervention) on Danish grade 4–10 pupils’ (aged 10–16 years) school-based and overall PA behaviours, school motivation, wellbeing, and academic achievement over the course of one school year in comparison to the schools’ usual practice. The schools’ usual practice typically involves indoor classroom-based activities. The intervention is the same well-described and manualised EOtC intervention that was investigated in the abovementioned quasi-experimental study, TEACHOUT [49]. See the MOVEOUT study Theory of Change, Fig. 1.

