### Evaluation of implementation

#### Design

Adherence to the intervention will be investigated in a repeated design with weekly monitoring of EOtC practised during the intervention in the intervention group and control group (Month 4 to Month 14, see Table 1). Quality of delivery, variations, facilitating and limiting contextual factors at school, local, and municipality level, and teachers’ acceptability of the intervention will be investigated through semi structured interviews [81] with intervention group teachers taking place in the second half of the implementation period (Month 10, see Table 1).

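### Post-tests at Months 10 to 12 are described as coming at the end of the school year and of the intervention, but EOtC runs to Month 14, so the timeline must be reconciled

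*Protocol article*

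**What the plan says.** - **Randomisation** gives the anchor: allocation took place "on 1st of April 2022 (Month 0, see Fig. 4").
- **Intervention** gives the delivery period: "for one schoolyear (in this study, August 2022 to June 2023, Month 4 to 14".
- **Evaluation of implementation, Design** agrees, with weekly monitoring "during the intervention in the intervention group and control group (Month 4 to Month 14, see Table 1"). Table 1 also agrees: its EOtC row is marked through the close-out column at 14 months.
- **Sub-study 1, Design** places the first physical activity (PA) post-measure later in the text but earlier in time: it "will commence during the end of the school year (Post-test A, Month 10 to 11"). The second is to be "assessed immediately before finalisation of the intervention (Post-test B, Month 11 to 12"). Table 1 puts the two post-tests at 10 and 11 months.
- The same section measures the H3 outcomes (school motivation, wellbeing, academic achievement) at Pre-test B and Post-test B only.
- It labels Pre-test A as Month -2 to -1 and Pre-test B as Month -1 to 0, but says that Pre-test B was collected after randomisation. The A/B pairs are there to deal with season.
- **Aims** states the comparison as one "over the course of one school year in comparison to" usual practice.

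**The concern.** The month numbers and the verbal descriptions of the post-tests point to different times, and the choice between them changes what the trial estimates.

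If the months are right, every Sub-study 1 outcome is taken while a fifth or more of the planned delivery is still to come, and the last months of EOtC contribute to no outcome. A statement about a full school year would then claim more exposure than was studied. This matters most for outcomes that may build up over time, such as reading and mathematics, which have a single follow-up. The main (per-protocol) analysis is also affected, because it keeps or drops classes on their average weekly EOtC over the whole school year. Part of that average would come from weeks after the outcome was measured.

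If the descriptions are right, the post-tests come after control teachers took the EOtC course in April 2023. Some contamination of the comparison is then possible, and the seasonal pairing with the pre-tests has to be shown rather than assumed.

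**Working it through.** **Step 1. Check the month scale.** Take Month 0 as April 2022 (Randomisation). Month 4 is then August 2022 and Month 14 is June 2023. This reproduces exactly the delivery period under Intervention, so the anchor and the delivery dates are consistent. Delivery lasts 14 - 4 = 10 months.

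**Step 2. Put the post-tests on that scale.** Elapsed EOtC is (month - 4), and its share of delivery is (month - 4)/10.

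| Point | Month | Calendar | Elapsed EOtC | Share | Still to come |
|---|---|---|---|---|---|
| Post-test A opens | 10 | February 2023 | 6 months | 60% | 4 months |
| A closes, B opens | 11 | March 2023 | 7 months | 70% | 3 months |
| Post-test B closes | 12 | April 2023 | 8 months | 80% | 2 months |
| Delivery ends | 14 | June 2023 | 10 months | 100% | 0 |

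The H3 outcomes, taken only at Post-test B, follow 7 to 8 of 10 months.

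**Step 3. Check sensitivity to how months are counted.** If delivery is counted to the end of June it lasts 11 months, and the shares become 6/11 = 55%, 7/11 = 64% and 8/11 = 73%. If Month 12 is read as the whole of April 2023, Post-test B closes after 9/11 = 82%, with May and June still to run. On each count at least two months of delivery follow the last measurement.

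**Step 4. Check the pre-test labels.** Adding 12 to the pre-test labels gives (-2 to -1) + 12 = 10 to 11 and (-1 to 0) + 12 = 11 to 12. By label, then, each post-test repeats its pre-test one year later. But a window running from Month -1 to Month 0 begins before 1 April 2022, whereas the text has Pre-test B collected after randomisation on that date. Label and description do not fully agree here either, so the seasonal match cannot be confirmed from the labels.

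**Step 5. Compare with control training.** April 2023 is Month 12. Under the month labels Post-test B closes at about that time. Under the descriptions both post-tests would probably follow it.

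**Step 6. Compare with the per-protocol rule.** The adherence average covers the school year. Under the month labels, 14 - 12 = 2 to 14 - 10 = 4 months of that average fall after the outcome measurement.

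**The case against.** The best defence is that the windows are sensible and only the wording is loose. By label they repeat the pre-tests 12 months later and are complete at about the time controls are trained. Table 1 openly marks EOtC as continuing through both post-tests to close-out, so the overlap is not hidden. The Intervention section also describes April 2023 as near the end of implementation, which suggests that the authors use such phrases broadly. This stands as a reason not to fault the choice of windows. It does not rescue the text: two to three remaining months out of ten is not immediately before the end, and the Aims still speak of one school year.

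Three stronger readings are tempting, and the document does not support them.

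- A reader might infer that the trial certainly measures only a partial year. That takes the month labels as fact, although the Pre-test B label conflicts with its own description. The design timeline (Fig. 4) is not available here to settle the matter.
- A reader might infer that later post-tests would break the seasonal match. The Design section names no calendar month for any test and the date of Pre-test B is uncertain, so this is not established.
- A reader might scale d = 0.374 by 0.7 to 0.8 and infer a loss of power. Under Sample size, that value is what the expected sample can detect. It is not a predicted full-year effect, and no build-up of effect over time is stated.

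**Conclusion.** The inconsistency is real. Randomisation, Intervention, Evaluation of implementation and Table 1 agree on delivery to Month 14. Post-tests at Months 10 to 12 therefore follow 6 to 8 of 10 months of EOtC (7 to 8 for H3) and cannot also fall at the close of the school year and of the intervention. These figures assume that the month labels are correct and that Month 0 is April 2022. Counting whole calendar months moves the shares to about 55% to 82% and does not change the conclusion.

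This is more than a slip of wording. It determines when every Sub-study 1 outcome is taken, what exposure the one-school-year claim rests on, and whether outcomes come before or after control teachers are trained. The document does not show which version is right, and the direction and size of any effect on the estimate cannot be computed from it.

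**What to change.** Give calendar dates for Pre-tests A and B and Post-tests A and B, and bring Sub-study 1 Design, Intervention and Table 1 into line with them, including the position of Pre-test B relative to randomisation. Then take one of two routes.

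- **If the month windows are right:** delete the two end-of-period descriptions. State the H1 to H3 objective and conclusion as the effect after about 6 to 8 months of EOtC (7 to 8 for H3). Base the per-protocol adherence average on EOtC delivered before the post-test.
- **If the descriptions are right:** correct the month numbers in the text and Table 1. Report that the post-tests followed the control teachers' course in April 2023, and how their season compares with that of the pre-tests.

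The sponsor holds the actual dates, so the cost is mainly wording. On the first route the adherence average must also be computed over a shorter period, and the claim may become less favourable: part of a school year instead of a whole one.

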#### Outcome measures

*School-based and overall PA behaviours* will be measured with Axivity® AX3 accelerometers (see full pre-registered study description of the investigation of PA behaviours [51]). All acceleration data will be processed in Matlab (Version 9.9.0 R2020b, Mathworks Inc., Natick, Massachusetts, US), which includes resampling, generating ActiGraph counts [58], identification of non-wear, and summarising the subjects’ time spent in different PA intensity domains and with types of PA behaviour as running, walking, standing, and sitting. Non-wear periods is identified from both acceleration and temperature using the method described in the study by Rasmussen et al. [59]. Pupils should have valid data from at least one pre-intervention PA measurement.

*School motivation* is measured using the Academic Self-Regulation Questionnaire (SRQ-A) [60]. The SRQ-A is a domain-specific 32-item self-report questionnaire developed for measuring the level of autonomy relative to doing different types of schoolwork among pupils in late primary and lower-secondary school. In this study, the items from the homework domain are omitted as not every school in Denmark uses homework.

*Wellbeing* will be measured using two different scales, the overall score from the KIDSCREEN-27 questionnaire and the pro-social behaviour scale of the Strengths and Difficulties Questionnaire (SDQ). KIDSCREEN-27 is the 27-item version of the KIDSCREEN Health-Related Quality of Life (HRQoL) questionnaire which measures the subjective health, wellbeing, and health-related quality of life of children aged 8–18 years [61]. The pro-social behaviour scale of the SDQ measures resources and functioning in terms of social skills and competences of children aged 11–17 years [62, 63], although high reliability was reported for use in pupils aged 10 years in a similar EOtC intervention study [26].

*Academic achievement* will be measured with two scales measuring reading competence and math skills. Reading competence will be measured with the validated age-adapted text reading test (Tekstlæseprøve, Grade 3–7; Tekstforståelse Udsagn A [Text comprehension Statement A], Grade 8–10) by Hogrefe [64]. Math skills will be measured with the validated age-adapted mathematical basic skills test (MG, Matematik Grunglæggende [Mathematics Basics]) by Hogrefe [65].

#### Sample size

Three classes were expected to drop-out during the intervention as per observations in the TEACHOUT study [38]. We further expected a sample size reduction by approximately 20% of the pupils due to drop-out and invalid accelerometer data (equivalent to four pupils per class). We expected an analytical sample of ~ 30 schools, ~ 51 classes, and ~ 867 pupils in total. The expected analytical sample allows 95% power to identify a small to medium effect size using a one tailed test (Cohen’s d = 0.374 95% CI [0.187,0.561]). Calculations accounted for intraclass correlations (ICC) derived from the TEACHOUT dataset of 0.046 within classes and 0.035 within schools. Power calculations were conducted using R package PowerUpR [66].

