### Data processing

All analyses will be processed in either RStudio or IBM® SPSS® Statistics with the level of statistical significance for all tests set to < 0.05.

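### The printed detectable effect of d = 0.374 does not follow from the 51 classes and 867 pupils it is tied to; the stated inputs give 0.381, a minor discrepancy

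*Protocol article*

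**What the plan says.** The protocol article's Recruitment and participants section plans 30 schools, 1.8 classes per school on average (54 classes) and 21 pupils per class, 1,134 pupils in all.

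The Sample size section of Sub-study 1 then makes two deductions. For classes: "Three classes were expected to drop-out during the intervention as per observations in the TEACHOUT study". For pupils: "approximately 20% of the pupils due to drop-out and invalid accelerometer data (equivalent to four pupils per class". It gives the result: "We expected an analytical sample of ~ 30 schools, ~ 51 classes, and ~ 867 pupils in total". The counts are consistent with each other: 54 − 3 = 51, 21 − 4 = 17, and 51 × 17 = 867.

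The next sentence attaches the power statement to that sample: "The expected analytical sample allows 95% power to identify a small to medium effect size using a one tailed test". The effect is printed as d = 0.374 with limits 0.187 and 0.561. The section says that the calculation accounted for ICCs of 0.046 within classes and 0.035 within schools and was run in PowerUpR. It mentions no covariate. The Data processing section describes the analyses "with the level of statistical significance for all tests set to < 0.05".

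**The concern.** The effect and its limits are given to three decimals and tied explicitly to the sample after drop-out. A reader who enters the printed inputs for that sample should recover them, and does not. The same inputs with the recruitment average of 1.8 classes per school recover all three figures. This looks as if one of the two announced deductions did not reach the calculation.

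This is the only power statement in the article, so it should be reproducible from what is printed. At stake is the accuracy of that one reported figure. The design and the chance of a usable answer are not affected.

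**Working it through.** **Inputs.** From Sample size: 30 schools (K), ICC 0.035 for schools, ICC 0.046 for classes, one-tailed test, 95% power. From Data processing: alpha 0.05, taken as one-tailed. From Randomisation: 1:1 allocation by school. Assumed because nothing else is printed: a three-level cluster design with treatment at school level, no covariates, and df = K − 2 = 28.

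**Formulas.** With C classes and N pupils, and 1 − 0.046 − 0.035 = 0.919 at pupil level:

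- SE = √{4 × [0.035/K + 0.046/C + 0.919/N]}
- detectable effect = (t₀.₉₅,₂₈ + t₀.₉₅,₂₈) × SE = 2 × 1.7011 × SE = 3.4023 × SE
- limits = detectable effect ± 1.7011 × SE

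**Step 1: the printed figures.** Take 54 classes of 17 pupils, N = 54 × 17 = 918.

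- SE = √{4 × [0.001167 + 0.000852 + 0.001001]} = 0.1099
- d = 3.4023 × 0.1099 = 0.3739
- limits 0.1870 and 0.5609

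All three agree with the print to three decimals.

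**Step 2: the sample named in the text.** Take 51 classes, N = 867.

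- SE = √{4 × [0.001167 + 0.000902 + 0.001060]} = 0.1119
- d = 3.4023 × 0.1119 = 0.3806
- limits 0.1903 and 0.5709

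None of the three agrees with the print. The difference in d is 0.3806 − 0.3739 = 0.0067.

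**Step 3: could rounding explain it?** Moving both ICCs across their rounding limits takes the 51-class value only from 0.379 to 0.382. The 54-class value runs from 0.372 to 0.375, which includes the printed figure.

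**Step 4: other counts, same formula.**

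| Classes × pupils per class | d |
|---|---|
| 51 × 17 | 0.381 |
| 51 × 18 | 0.377 |
| 54 × 17 | 0.374 |
| 51 × 21 | 0.368 |
| 54 × 21 | 0.362 |

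**Step 5: other routes to 0.374.** The cause cannot be settled from the article, because other inputs also give the printed figures:

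- 51 classes of 17 pupils with a pupil-level R² of 0.10: the last term becomes 0.919 × 0.90/867 = 0.000954, SE = 0.10996, d = 0.3741, limits 0.1871 and 0.5612.
- The same 51 classes with an R² of about 0.035 at all three levels: d = 0.3739.
- ICC labels swapped, two classes per school (60 classes) and 17 pupils: d = 0.3738, limits 0.1869 and 0.5607.

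**Step 6: power of the named sample at d = 0.374.** The ratio is 0.374/0.1119 = 3.343. Subtracting 1.701 leaves 1.642, which on 28 df is 94.4%. The noncentral t gives 94.7%. With 54 classes the same two methods give 95.0% and 95.3%.

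**The case against.** The strongest reply is that nothing of substance is wrong. The sample counts are marked as approximate, the ICCs come from an earlier study, and 94.4% to 94.7% is 95% for planning purposes. This stands. It bears on how much the discrepancy matters, not on whether it exists: the approximation signs qualify the counts, while the effect and its limits are printed to three decimals for a named sample.

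A second reply is that the software call is not shown and the planned models adjust for pre-test score, sex and age, so an R² may have been entered. This also stands, and it is why the omitted class loss is an inference. The article describes the calculation only through its ICCs, however, so the figure still cannot be recovered from what is printed. The swapped-ICC route is less plausible, since it needs 60 classes, a number found nowhere in the article.

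A reader might go further in three ways that the document does not support:

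- **That 0.374 can come only from 54 classes.** Step 5 shows that it cannot be tied to one set of inputs.
- **That the trial's true detectable effect is larger than stated.** The value 0.381 assumes that covariates explain nothing. Under assumed R² values of 0.25 to 0.50 at all levels, 51 classes would give 0.3806 × √0.75 = 0.33 down to 0.3806 × √0.50 = 0.27. For the adjusted analysis, 0.374 may be conservative.
- **That whole schools must also be deducted.** Single-class schools are allowed, but nothing says that the lost classes would be a school's only class, and the school count is itself approximate. Even with 27 schools the figure would be 0.390.

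**Conclusion.** The point holds as a minor reporting inconsistency. On the printed inputs, with one-tailed alpha 0.05, a three-level design and no covariates, the named sample of 30 schools, 51 classes and 867 pupils has a detectable effect of 0.381 [0.190, 0.571], not 0.374 [0.187, 0.561]. The most natural explanation is that 1.8 classes per school was carried over from the recruitment plan while pupils per class were reduced to 17. An undisclosed covariate R² would explain the figures equally well.

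The gap is 0.007 in d, or 0.3 to 0.6 percentage points below 95% power at d = 0.374. The stated power is therefore essentially right for the stated sample, the effect is still small to medium, and no decision on design, recruitment or analysis depends on the difference.

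**What to change.** Change one sentence in the Sample size section, in whichever of these ways is true:

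- give d = 0.381 [0.190, 0.571] for 30 schools, 51 classes and 867 pupils, without covariates;
- say that 0.374 [0.187, 0.561] refers to 54 classes and 918 pupils, after pupil loss but before class drop-out; or
- keep 0.374 for the 51 classes and state the R² that was entered and at which level.

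Showing the PowerUpR inputs would settle which applies. The cost is a corrected or annotated number. Under the first option the detectable effect becomes slightly less favourable; nothing in the conduct of the trial changes.

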**Fig. 2 Fig2:**
[figure not shown]
Illustrations of the hypotheses of the two sub-studies

#### Sub-study 1

Effects of EOtC (see full pre-registered protocol for H1 and H2 ([51]).

H1 Pupils in the intervention group will retain higher PA intensities compared to the control group, specifically a) more MVPA, b) more LPA, and c) less SED time (referred to in the following only as PA intensities).H2 Pupils in the intervention group will retain a) more running, b) more walking, c) more standing, and d) less sitting time compared to the control group.H3 Pupils in the intervention group will achieve higher school motivation, wellbeing, and academic achievement compared to the control group.

#### Sub-study 2

Mechanisms of EOtC. The unit of analysis is schooldays or sessions.

H4 EOtC schooldays or sessions will be associated with higher PA intensities, higher levels of intrinsic motivation, and more positive perceptions of the teaching environment compared to usual schooldays or sessions.H5 The pedagogical and didactical elements during EOtC sessions will be different from the pedagogical and didactical elements during usual sessions.H6 The expected association between EOtC and PA intensities, intrinsic motivation, and perceptions of the teaching environment will be mediated by the pedagogical and didactical elements of the EOtC sessions.

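### The 95% power rests on a one-tailed test, but the analysis rule sets 0.05 for all tests without a direction; two-sided and unadjusted, power at d = 0.374 is about 90%

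*Protocol article*

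**What the plan says.** All references are to the protocol article.

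- **Sample size (Sub-study 1).** "We expected an analytical sample of ~ 30 schools, ~ 51 classes, and ~ 867 pupils in total". For this sample the section claims: "The expected analytical sample allows 95% power" to "identify a small to medium effect size using a one tailed test", and gives "Cohen’s d = 0.374 95% CI [0.187,0.561" in brackets. The intraclass correlations are 0.046 for classes and 0.035 for schools. This is the only mention of tails in the article.
- **Statistical analyses (Sub-study 1).** H1 to H3 are analysed with linear mixed models that take account of pre-test scores and have random effects for class and school. No direction of test is given. For H1 and H2 the reader is sent to a pre-registration for further modelling detail; for H3 the base model is set out in the article.
- **Data processing.** One rule covers every analysis: "level of statistical significance for all tests set to < 0.05". Again no direction is given.
- **Sub-studies and hypotheses.** H1 to H3 are worded as improvements in the intervention group. H5, in Sub-study 2, has no direction: the elements "will be different from the pedagogical and didactical elements during usual sessions".
- **Background.** Among the limitations of the earlier TEACHOUT study, the article lists that its data did not allow potential adverse effects to be investigated.

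**The concern.** The power statement and the decision rule are not tied to the same test. A significance level of 0.05 with no direction is commonly read as two-sided, and the power claim was not computed for a two-sided test. The article leaves two readings open, and each has a consequence.

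- **Two-sided at 0.05:** the 95% figure belongs to a different test, and the power at the stated effect is lower unless covariates make up the difference.
- **One-tailed at 0.05:** the chance of a false claim of benefit is 5%, against 2.5% per direction for a two-sided 5% test. A fall in wellbeing, reading or mathematics could be seen in the estimate but not formally concluded.

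The second consequence weighs most on H3. The intervention moves at least five hours of teaching a week out of the classroom, and the article itself presents adverse effects as an open question. While the direction is unstated, the tail could also be chosen after the data are seen.

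**Working it through.** **Inputs, all from the article.** K = 30 schools; 51 classes, so J = 51/30 = 1.7 classes per school; 867 pupils, so n = 867/51 = 17 pupils per class; school ICC 0.035; class ICC 0.046; 1:1 allocation, so P = 0.5; effect d = 0.374; level 0.05.

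**Assumptions, because the article gives none.** Covariate R² = 0; t distribution with K − 2 = 28 degrees of freedom.

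**Formula (three-level cluster-randomised design).**

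SE = √{ [ICC_school/K + ICC_class/(KJ) + (1 − ICC_school − ICC_class)/(KJn)] / [P(1 − P)] }

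Detectable effect = SE × (t for the level + t for the power). Power at a given d comes from the noncentral t distribution with noncentrality d/SE.

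**Step 1: standard error for the stated sample.**
- School term: 0.035/30 = 0.001167
- Class term: 0.046/51 = 0.000902
- Pupil term: 0.919/867 = 0.001060
- Sum 0.003129; divided by 0.25 this is 0.01251; SE = 0.1119

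**Step 2: reproduce the article's figure (one-tailed 0.05).**
- Detectable effect at 95% power: 0.1119 × (1.701 + 1.701) = 0.381
- Power at d = 0.374 (noncentrality 0.374/0.1119 = 3.34): 94.7%

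With the 1.8 classes per school given for recruitment (54 classes) and 17 pupils per class, SE = 0.1099 and the detectable effect is 0.1099 × 3.402 = 0.374, the printed value. The printed interval fits as well: its half-width, 0.374 − 0.187 = 0.187, is exactly half of 0.374. That ratio arises when the two t quantiles are equal, as with one-tailed 0.05 and 95% power. A two-tailed calculation would give 2.048/(2.048 + 1.701) = 0.546. The one-tailed basis is therefore confirmed by the figures as well as by the wording.

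**Step 3: the same samples tested two-sided at 0.05.**

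| Sample | SE | Power at d = 0.374 | Effect detectable at 95% power |
|---|---|---|---|
| 51 classes, 867 pupils | 0.1119 | 89.7% | 0.1119 × (2.048 + 1.701) = 0.42 |
| 54 classes, 918 pupils | 0.1099 | 90.7% | 0.1099 × 3.750 = 0.41 |

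**Step 4: sensitivity to baseline adjustment.** Stated sample, two-sided 0.05, d = 0.374. The R² values are assumptions; each variance term in Step 1 is multiplied by 1 − R² at its level.

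| Assumed R² | Two-sided power |
|---|---|
| 0 | 89.7% |
| 0.1 at all levels | 92.5% |
| 0.2 at all levels | 95.0% |
| 0.3 at all levels | 97.1% |
| 0.3 at pupil level only | 92.6% |
| 0.5 at pupil level only | 94.3% |

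**The case against.** Several arguments on the other side have force.

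- **Nothing contradicts.** A one-tailed test at 0.05 satisfies both the Sample size section and Data processing, and H1 to H3, the hypotheses of the sub-study being powered, are all directional. This stands. A reader might infer that the power claim and the decision rule clash outright; the text does not support that, because the rule is silent on direction.
- **H5 proves little.** A reader might take the undirected H5 as evidence that all tests are two-sided. H5 is a within-subject question in Sub-study 2 and is not what the Sample size section powers. It shows only that a one-tailed reading does not suit every test under the common rule.
- **The pre-registration may settle the direction for H1 and H2.** It may, and it is not shown. The article does not cite it for H3, whose base model is given without a direction.
- **The planned models adjust for the pre-test score.** This stands. A reader might infer that the trial fails to deliver its stated power. That does not follow: 89.7% is the figure with no covariate R², and an assumed R² of 0.2 at all levels brings two-sided power back to 95.0%. The article states no R², so neither figure can be called the planned one.
- **About 90% is still high power, and a one-sided 5% level is a disclosed choice.** Both are true, and an adverse estimate would still be visible. What a one-tailed test removes is the formal conclusion of harm.

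**Conclusion.** The point holds as an unreconciled mismatch between the test that was powered and the test that will be applied. It is not a proven contradiction, and it does not show an underpowered trial. With 30 schools, 51 classes, 867 pupils, the stated ICCs, 28 degrees of freedom and no covariate R², moving from a one-tailed to a two-sided 5% test lowers power at d = 0.374 from 94.7% to 89.7%, about 5 percentage points, and puts the effect detectable with 95% power at about 0.42. Baseline adjustment could recover part or all of this, depending on an R² that the article does not give.

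The stronger reason to settle the direction is H3: a one-tailed test could not formally conclude a fall in wellbeing or achievement, and the article itself identifies adverse effects as a gap to be filled.

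**What to change.** 1. In Statistical analyses for Sub-study 1 and in Data processing, state before analysis that the efficacy tests for H1 to H3, H3 above all, are two-sided at 0.05.
2. Restate the Sample size section for that test: for 30 schools, 51 classes and 867 pupils with no covariate R², about 90% power at d = 0.374, or 95% power at about d = 0.42.
3. If the power is meant to rely on baseline adjustment, give the R² assumed at each level and its source, and compute the figure from it.

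The cost is a few sentences and a slightly less favourable stated power. Enrolment and data collection do not change. The gain is that no choice of tail remains open once the data are seen, and the trial can conclude in either direction.
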